## Abstract

**Introduction:**

Depression is a leading cause of disability worldwide, affecting up to 300 million people globally. Despite its high prevalence and debilitating effects, only one-third of patients newly diagnosed with depression initiate treatment. Electronic cognitive behavioural therapy (e-CBT) is an effective treatment for depression and is a feasible solution to make mental health care more accessible. Due to its online format, e-CBT can be combined with variable therapist engagement to address different care needs. Typically, a multi-professional care team determines which combination therapy most benefits the patient. However, this process can add to the costs of these programs. Artificial intelligence (AI) has been proposed to offset these costs.

**Methods:**

This study is a double-blinded randomized controlled trial recruiting individuals experiencing depression. The degree of care intensity a participant will receive will be randomly decided by either: (1) a machine learning algorithm, or (2) an assessment made by a group of healthcare professionals. Subsequently, participants will receive depression-specific e-CBT treatment through the secure online platform. There will be three available intensities of therapist interaction: (1) e-CBT; (2) e-CBT with a 15–20-min phone/video call; and (3) e-CBT with pharmacotherapy. This approach aims to accurately allocate care tailored to each patient’s needs, allowing for more efficient use of resources.

**Discussion:**

Artificial intelligence and providing patients with varying intensities of care can increase the efficiency of mental health care services. This study aims to determine a cost-effective method to decrease depressive symptoms and increase treatment adherence to online psychotherapy by allocating the correct intensity of therapist care for individuals diagnosed with depression. This will be done by comparing a decision-making machine learning algorithm to a multi-professional care team. This approach aims to accurately allocate care tailored to each patient’s needs, allowing for more efficient use of resources with the convergence of technologies and healthcare.

**Ethics:**

The study received ethics approval and began participant recruitment in December 2022. Participant recruitment has been conducted through targeted advertisements and physician referrals. Complete data collection and analysis are expected to conclude by August 2024.

**Clinical trial registration:**

ClinicalTrials.Gov, identifier NCT04747873.

## Introduction

1

Depression is a leading cause of disability, affecting approximately 3.8% of the population worldwide (1, 2). Despite the high prevalence and negative consequences of depression, only one-third of individuals receive treatment, and three in five receive sufficient care (3, 4). In 2018, mental health care needs for 2.3 million Canadians were reported to be insufficient with 78.2% indicating reasons relating to accessibility (e.g., lack of knowledge on how to get help, financial issues, and time restraints) to be the top barrier to receiving mental health care (5). Another major hindering factor in patients’ access to effective mental health support is the cost of care (6). This outlines the importance of developing evidence-based and cost-effective solutions to address these issues on mental health care accessibility and efficiency.

Electronic cognitive behavioural therapy (e-CBT) is a good candidate to make mental health care more accessible and is effective in treating various mental health issues including mood and anxiety disorders (7–11). However, this internet-based treatment presents problems of high dropout rates and non-adherence (12). Treatment compliance is an important factor for positive psychotherapy treatment outcomes (13, 14). Drop-out rates for in-person psychotherapy vary from 20–47% depending on the study design (15–17), whereas a systematic review of 29 studies revealed the dropout rate for e-CBT for depression can range from 0–63%, with an average dropout rate of 32% (18). Multiple factors can affect patient compliance such as patient age, education, treatment engagement, and clinician involvement (12, 19, 20).

Furthermore, while pre-designed e-CBT content can make mental health care more scalable and affordable and address the general concerns of most individuals with mild to moderate symptoms (8, 9, 21, 22), individuals with severe symptoms may require further intensive clinical interventions and clinician involvement (22, 23). Stratified care begins treatment by matching care intensity (i.e., low vs. high intensity) based on the patient’s needs. Stratified psychiatry is beneficial because it can increase treatment response and remission rates by allocating treatments effectively (24). An important challenge in using a stratified care strategy is recognizing which group each patient belongs to and which resources are required to address their needs.

Currently, clinical decision-making is conducted by a multi-professional care team which can consist of a psychiatrist, residents, nurses, clinical psychologist, social worker, counsellor, and support worker (25). Although this collaboration is beneficial in many respects (26), is typically costly and results in long wait times (6). A previous framework using real patient data has demonstrated the cost-effectiveness of using machine learning in clinical decision-making (27). The use of machine learning in healthcare has significantly increased over the past few years. In the context of clinical decision-making, machine learning algorithms use large data sets from an array of sources to assist healthcare providers in making rapid and informed decisions (28). To further understand symptom severity and increase treatment efficacy, many researchers have tried to implement supervised machine-learning approaches to identify patient characteristics that may be associated with poor treatment outcomes and develop a treatment for patients (29–32). These novel decision-making algorithms aim to mimic human decision-making to help with objective and accurate evaluation of each patient’s needs (33). This technology can make personalized care a possibility, particularly in cases where clinical decision-making by a care team is not feasible or results in prolonged wait times. Overall, the novelty of machine learning in healthcare demands greater exploration and understanding of responsible use (34).

The goal of this study is to develop a machine learning algorithm that can identify the intensity of care an individual needs based on their probability of dropping out from treatment. This algorithm is expected to be comparable to the clinical decision-making process. It is expected to indicate the appropriate level of care for an individual experiencing depression to make treatment efficient and effective. We believe that the integration of AI-driven clinical decision-making would make mental health care delivery more scalable, accessible, and affordable while remaining highly personalized and effective. To make this possible, we need to (1) make objective and quantified evaluations of patients’ mental status and their needs, (2) utilize a decision-making algorithm that allocates the right level of care for each patient, and (3) demonstrate that this method of care delivery can enhance the quality of mental health care and reduce costs.

## Objectives

2

The primary objective of this study is to evaluate the effectiveness of the suggested level of care made by the AI compared to the healthcare team and the effectiveness of the stratified care model. This will be assessed using the change in the severity of depressive symptoms using the Patient Health Questionnaire – 9 Item (PHQ-9) (35) and Quick Inventory of Depressive Symptoms (QIDS) (36) scores, and the quality of life and functioning using Assessment of Quality of Life (AQoL-8D) (37) scores between the start and the end of the 13-session e-CBT program.

The secondary objectives include evaluating compliance and treatment completion using the number of sessions completed by each participant and evaluating the time and cost commitment of initial assessments (i.e., manual participant stratification by the healthcare team vs. the AI) and the different care intensities (i.e., only e-CBT, e-CBT + phone calls, or e-CBT + video calls). We will also evaluate the functional consequence of our interventions on participant quality of life via Quality-adjusted life years (QALY)s (38). Throughout the study, QALY estimates will be derived from AQoL-8D scores using the area under the curve method (39, 40). Outlined below are the research questions and the corresponding study hypotheses:

1 Will participants with major depressive disorder (MDD) assigned to an e-CBT program by an AI show similar outcomes in depressive symptoms at 3 months to those allocated to an e-CBT program decided by a team of healthcare professionals?

– We hypothesize that the outcomes in depressive symptoms of treatment arm 1 will be comparable to the outcomes of treatment arms 2 and 3 following e-CBT treatment.

2 How does AI-based clinical decision-making compare to that of a multi-professional healthcare team when allocating individuals with depression to an e-CBT program with different degrees of care intensity?

– We hypothesize that AI-based clinical decision-making (treatment arm 2) will provide suggestions comparable to that of a multi-professional care team (treatment arm 1).

3 Is this novel AI approach to e-CBT time and cost-efficient and comparable to the standard multi-professional healthcare decision-making team?

– We hypothesize that the AI approach will decrease the overall time and cost commitment of providing e-CBT.

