### Participants

3.1

Participants (*n* = 186: *n* = 31 per e-CBT group * 2 arms) will be recruited at Queen’s University from outpatient psychiatry clinics at both Kingston Health Sciences Centre sites (Hotel Dieu Hospital and Kingston General Hospital), as well as Providence Care Hospital in Kingston, Ontario. Additionally, self-referrals and referrals from family doctors, physicians, and clinicians across Ontario will be accepted. After obtaining informed consent from the participant, the participant will be evaluated using the Mini International Psychiatric Assessment (MINI) through a secure video appointment to confirm a diagnosis of MDD using the Diagnostic and Statistical Manual of Mental Disorders, Fifth Edition (DSM-5) (41), by a trained professional on the research team.

All eligible participants will be randomized to receive a treatment plan based on the decision of either the healthcare team (Arm 1) or the Triage Module using an AI algorithm (Arm 2). Participants will be randomly allocated to one of the two arms of the study by a research assistant on the team who will also balance the group based on demographic variables (i.e., sex, gender, age, and income). Participants and therapists in the study will be blinded to which treatment arm the participant belongs to. By the nature of this study, participants and therapists will not be blinded to which treatment intensity the participant will receive since it will be evident whether the participant is receiving a phone/video call in addition to usual e-CBT care or pharmacotherapy. Each participant will be provided with an effective form of treatment (i.e., e-CBT) regardless of which group they will be allocated to. Participants will be informed that there is no incentive to join the program and that joining or withdrawing at any point will not affect them negatively. It will also be explained to the participants that the program is not a crisis resource and that they will not always have access to their therapists. In the case of an emergency, participants will be directed to proper resources, and this event will be reported to the study’s lead psychiatrist (principal investigator). All data will be anonymized and analyzed by research team members who are not directly involved in the patient’s care.

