### Study design

3.3

If eligible for this randomized controlled trial, participants (*n* = 186) will be randomized (Figure 1) to receive an e-CBT treatment recommended by a multi-professional healthcare team consisting of a psychiatrist, psychiatric medical resident, and a trained research assistant (Arm 1, control group; *n* = 93), or the AI machine learning algorithm (Arm 2, experimental group; *n* = 93; Figure 1). To ensure blinding, all participants will complete the intake assessment by the healthcare team (Arm 1) and the Triage Module (Arm 2). Only the relevant data (i.e., Arm 1: intake assessment vs. Arm 2: Triage Module) will be analyzed depending on the treatment arm that the participant is randomly assigned to.

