#### Treatment arm 1: healthcare team allocation

3.3.1

Allocation of treatment intensity by the multi-professional healthcare team will be based on the following criteria:

The severity of symptoms/disability (DSM-5 criteria).Mental health factors (prior treatments and responses, current and past psychotic/manic episodes, current and past suicidal/homicidal ideation/attempts, family mental health history, past psychiatric history, and hospital admissions).Medical factors (current medical conditions and medications, personal and family medical history).Social factors (support system and living situation, and occupational, social, and personal functional impairment).

To assess the severity of MDD symptoms and the functional impairments, participants will complete the PHQ-9 and Sheehan Disability Scale (SDS) (42, 43) before the assessment appointment. The trained research assistant on the multidisciplinary team will conduct the assessment appointment and will relay the information to the rest of the team later to deliberate on treatment intensity allocation. All assessments will occur virtually through phone and video calls. Together, the healthcare team will decide whether the participant should be assigned to the e-CBT-only treatment, e-CBT treatment with weekly phone/video calls, or e-CBT treatment with pharmacotherapy. This process mimics the current triage process in clinical settings. To track cost-effectiveness, the trained research assistant will track the total duration of the individual assessment and team deliberation meetings for analysis of the total time commitment per patient.

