To gather the relevant data (i.e., participant compliance and change in depression severity, as evaluated by the PHQ-9), the Triage Module was designed. As previously explained, NLP of the participants’ written accounts of their challenges with depression in the Triage Module will be used to calculate a Symptomatic Score. To verify the AI’s treatment allocation logic, completion rate and the change in PHQ-9 scores in a sample of participants (*n* = 190) who were previously enrolled in e-CBT-only treatment was assessed. The decision-making algorithm determined that the e-CBT-only program was suitable for 62 of the 190 participants (32.63%). Within these 62 participants, 53.22% (*n* = 33) had completed the e-CBT-only program in its entirety and only 20% (*n* = 12) had a final PHQ-9 score > 14. Furthermore, the algorithm indicated that e-CBT with telephone calls would be suitable for 100 out of the 190 participants (52.63%). Of the 100 participants, 41.0% (*n* = 41) completed the whole round of e-CBT-only therapy and 31.0% (*n* = 31) had a final PHQ-9 score > 14. Lastly, the algorithm indicated that e-CBT with video call was appropriate for 28 out of 190 participants (14.74%). Of these 28 participants, 35% (*n* = 10) completed the whole round of e-CBT-only therapy and 40% (*n* = 11) had a final PHQ-9 score > 14. The logic of the AI’s decision is therefore justified as those participants allocated to the e-CBT-only group had the highest percentage of completion and lowest percentage of final PHQ-9 scores >14 when completing e-CBT-only. Therefore, minimal therapist intensity is required for these individuals and e-CBT-only is sufficient. Conversely, participants allocated to the e-CBT with video call had the lowest completion rates and highest rates of final PHQ-9 scores >14 when enrolled in e-CBT-only. These findings justify the AI’s logic that greater therapist interaction is required. It is also important to note that demographic factors like age (below or above 40 years), biological sex (male or female) and income (less or more than CAD 50,000) did not have any significant effects on the number of sessions completed by participants (*p* = 0.92, 0.18, 0.90 for age, sex, and income respectively). The demographic factors did not affect the change in PHQ-9 score (i.e., the difference between the beginning and end of treatment scores) either (*p* = 0.20, 0.46, 0.39 for age, sex, and income respectively).

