### Sample size determination

3.10

In our previous clinical trials and gathered data (47), the average PHQ-9 score changed from 16.2 before e-CBT to 11.48 after 12 sessions of e-CBT (joint standard deviation; SD = 5.45). Based on these numbers, the effect size (Hedges’ G) is equal to 0.86. Given the effect size and a power of 0.8, we would need 14 participants to observe a significant effect in a paired sample *t*-test. Considering the completion rate of 45%, we would require 31 participants in each group to observe significant results. Given the two treatment arms and three treatment intensities, we would require 186 participants to detect significant clinical change across all groups. We believe this sample size is large enough to perform further analyses on factors such as the role of sex and gender in treatment efficacy and completion rate.

To follow up on this sample size determination, we will use previously collected data as mentioned above to simulate the population and use a random sampling method to determine the effect size for our power calculation. We will do this by simulating a population based on the mean and standard deviation of our previous e-CBT studies and collecting data, then randomly sampling participants to each treatment arm. This simulation will be developed using Python code. Based on this random sampling, we will calculate the effect size, set the power of 0.8, and consider the completion rate of 45% to determine the sample size required to detect a significant clinical change across the groups.

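### The primary objective's clause on the effectiveness of the stratified care model cannot be answered, because both randomised arms are stratified and no analysis has an unstratified comparator

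*Protocol article*

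**What the plan says.** - **Objective.** Section 2 of the protocol article has one primary objective with two parts: the AI's suggested level of care "compared to the healthcare team and the effectiveness of the stratified care model". Both are to be judged on PHQ-9, QIDS and AQoL-8D "scores between the start and the end of the 13-session e-CBT program".
- **What is randomised.** Section 3.1 says participants are "randomized to receive a treatment plan based on the decision of either the healthcare team (Arm 1) or the Triage Module using an AI algorithm". Section 3.3 puts 93 in each arm; Arm 1 is "to receive an e-CBT treatment recommended by a multi-professional healthcare team".
- **What each arm then does.** In Arm 1 (section 3.3.1), "the healthcare team will decide whether the participant should be assigned to the e-CBT-only treatment, e-CBT treatment with weekly phone/video calls", or e-CBT with pharmacotherapy. In Arm 2 (section 3.3.2) the algorithm picks among the same three levels from PHQ-9 and a Symptomatic Score. Section 3.1 adds that everyone receives e-CBT.
- **Hypotheses and analyses.** Hypothesis 1 expects that outcomes of "treatment arm 1 will be comparable to the outcomes of treatment arms 2 and 3 following e-CBT treatment", and the heading of section 4.1 repeats the three-arm wording. The design has two arms. The outcome model in section 4.1 crosses 2 arms, 3 care levels and 3 time points.
- **Earlier data.** Section 3.10 sizes the trial on a paired test, because "the average PHQ-9 score changed from 16.2 before e-CBT to 11.48 after 12 sessions of e-CBT". Section 3.3.2 separately reports that the algorithm's logic was checked "in a sample of participants (*n* = 190) who were previously enrolled in e-CBT-only treatment was assessed".

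**The concern.** Effectiveness of a care model is a comparative claim. The Introduction treats it so: it says stratified care can raise response and remission, and lists showing that this way of delivering care improves quality among the things the team needs to do. A comparative claim needs a group that did not get the model, and this trial enrols none.

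The randomised factor is who chooses the intensity. That answers AI versus team. It cannot say whether choosing an intensity for each patient is better than giving everyone the same care.

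At stake is one part of a primary objective. A positive-looking result for it is likely even if stratification adds nothing, because natural course and the ordinary gain from e-CBT both enter start-to-end change. Differences between care levels offer no way round, since the levels are chosen on how ill the patient is. An unseen analysis plan could not repair this, because it cannot supply participants who were never enrolled.

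**Working it through.** **1. Is there an unstratified group?**

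| Source (protocol article) | Contrast available |
|---|---|
| 3.1, 3.3 | Arm 1 v Arm 2: who chooses the level |
| 3.3.1, 3.3.2, 3.4 | Same three levels in both arms; level assigned by need, not at random |
| 4.1 | 2 × 3 × 3 model: arm, level, time; no unstratified level |
| 4.2 | Agreement between AI and team decisions |
| 4.3 | Cost by arm and level |

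No row compares stratified with unstratified care. The 190 earlier e-CBT-only participants appear only as a check of the algorithm's logic, and section 4 does not use them.

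**2. The plan's own sample size.** Inputs from section 3.10: means 16.2 and 11.48, SD 5.45, power 0.8, completion 45%. Section 4 gives a significance level of 0.05; two-sided is assumed.

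- Change: 16.2 − 11.48 = 4.72. Effect size: 4.72 / 5.45 = 0.866 (stated 0.86).
- Paired t-test, exact noncentral t: 13 completers give power 0.817 and 14 give 0.849 (stated 14).
- 14 / 0.45 = 31.1, stated as 31 per group; 31 × 6 = 186.

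The figures reproduce to within one participant. They describe an uncontrolled before-after test in each of six groups.

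**3. What that test shows if stratification adds nothing.** Assume participants repeat the 4.72-point change and, as the plan does, treat 5.45 as the SD for the paired test.

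- 14 completers (one group): power 0.85.
- 42 completers (one arm, 0.45 × 93 = 41.9): power above 0.999.
- Half the change (effect size 0.433), 42 completers: power 0.78.

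A significant fall is therefore expected without any benefit of stratification.

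**4. Contrasts between care levels.** Section 3.3.1 bases the Arm 1 level on severity, history, and medical and social factors. Section 3.3.2 bases the Arm 2 level on PHQ-9 and the Symptomatic Score. Both are confounded by indication.

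In Arm 2, e-CBT-only requires PHQ-9 below 19 and pharmacotherapy requires PHQ-9 above 19, so these two levels are sorted on the outcome measure. As an illustration, assume normal scores with mean 16.2 and SD 5.45, sorting on PHQ-9 alone, and the sorting score used as baseline. With continuity-corrected cuts at 19.5 and 18.5:

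- Mean above the cut 22.84, which is 6.64 above 16.2; mean below the cut 13.20, which is 3.00 below it.
- Expected drift is (1 − r) × distance from the mean.
- r = 0.8: 0.2 × 6.64 = 1.33 down and 0.2 × 3.00 = 0.60 up; gap 1.9.
- r = 0.6: 0.4 × 6.64 = 2.66 down and 0.4 × 3.00 = 1.20 up; gap 3.9.

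The correlations are assumed; the protocol gives none.

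**The case against.** The strongest reply is that this is one loose clause. All three research questions and hypotheses concern AI versus team, section 4.1 opens by comparing Arm 1 with Arm 2, and no analysis claims to test stratification. This stands as a limit on the point. It also confirms the point, because a clause in the primary objective has no hypothesis, comparator or analysis behind it.

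Four stronger readings are tempting, and the document does not support them.

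- A reader might infer that the investigators plan to credit before-after gain to stratification. No section says so. The most that can be said is that the design offers no better evidence for the clause.
- A reader might take the 4.72-point fall as the change seen without stratification. Section 3.10 says only that it came from earlier trials and gathered data on e-CBT and does not describe how care was allocated. The e-CBT-only label belongs to the 190 in section 3.3.2, and nothing says the two samples are the same.
- A reader might take 2 to 4 points as the regression effect across the trial. It applies at most to the top versus bottom level of Arm 2. The Symptomatic Score also sorts, the middle level mixes high and low PHQ-9 scores, Arm 1 has no PHQ-9 cut-off, and 5.45 is called a joint SD. The drift shrinks if the analysed baseline is a separate administration from the sorting score.
- A reader might see the mention of a third arm as evidence of a lost comparator. It shows only that the labelling disagrees with the two-arm design.

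**Conclusion.** The point holds in limited form. The stratified-care part of the primary objective cannot be answered by this design. That conclusion follows from the structure of the arms and analyses and needs none of the calculations.

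The figures only show how easily a misleading positive could arise: a power of 0.85 per group of 14 and above 0.999 per arm of 42 if the earlier change recurs. These rest on the plan's own effect size, a two-sided 0.05 level and 45% completion. The regression gap of about 2 to 4 points is an illustration under the stated assumptions, not an estimate for this trial.

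The randomised AI-versus-team comparison is unaffected. The clause should still be corrected, because it alters what the trial may conclude on a primary objective and the correction costs almost nothing.

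**What to change.** 1. In section 2, remove the clause on the effectiveness of the stratified care model from the primary objective, or restate it as a descriptive aim, so that the primary question is Arm 2 versus Arm 1. Correct the reference to a third arm in Hypothesis 1 and in the heading of section 4.1.
2. In section 4.1, state that within-group change and differences between care levels are descriptive and do not estimate the effect of stratification or of intensity.

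The cost is a change of wording and a narrower claim. No participant, visit or treatment changes.

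A comparison with the 190 earlier e-CBT-only participants is optional and not part of the required change. If it is done, it should:

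- be labelled non-concurrent and non-randomised;
- account for the third level, which section 3.3.2 describes as video call for the 190, while the allocation rule in the same section and section 3.4 give pharmacotherapy for the trial (these passages need reconciling);
- say that the same 190 were used to verify the algorithm;
- amend the statement in section 3.3 that only the data relevant to the assigned arm are analysed, since Triage Module output would be needed for Arm 1 as well.

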## Statistical analysis

4

Initially, all data will be examined for missing, nonsensical, and outlying variables. Missing data will not be attributed and will be treated as missing. All statistical analyses will be performed at the end of the trial and will consider a significance level of 0.05 and 95% confidence intervals. Analyses will be conducted to account for and assess differences across sex and gender identifications, and how these factors affect the adaptability and efficacy of e-CBT.

### Hypothesis 1: outcomes in depressive symptoms of treatment arm 1 will be comparable to treatment arms 2 and 3

4.1

Clinical outcomes of the healthcare teams’ decision (arm 1) versus the AI’s decision (arm 2), will be compared by assessing the treatment completion rate, number of completed sessions, and change in questionnaire scores. The completion rate across the two study arms and three levels of care will be calculated using a 2 × 3 × 2 contingency matrix (i.e., healthcare team vs. AI × 3 different treatment intensities × completers vs. dropouts) and chi-square analysis to compare within and between completion rates in the two arms. We will use a 2 × 3 (i.e., healthcare team vs. AI × 3 different levels of care) two-way analysis of variance (ANOVA) to compare the number of completed sessions across participant groups and care levels. Questionnaires are collected at 3 different times; at the start (for all participants), midway (for those who completed at least 6 sessions), and end of the study (for those who completed the treatment program). We will use a 2 × 3 × 3 (i.e., healthcare team vs. AI × 3 different levels of care × 3 time points) linear mixed-effects model for each questionnaire to compare clinical outcomes within and between groups and times. A mixed-effects model analysis will account for any missing data caused by participant dropout. Finally, we will assess if demographic covariables affect clinical outcomes using multiple 2 × 2 × 3 × 3 (demographic factors (e.g., male vs. female) × healthcare team vs. AI × 3 different levels of care × 3-time points for the questionnaire’s score) mixed-effects model to account for each demographic variable (i.e., sex, gender, age, and income). Bonferroni corrections will follow the ANOVA analyses in *post hoc* analyses.

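### PHQ-9, QIDS and AQoL-8D are unranked primary measures, each tested at 0.05 in its own model, with no rule for which scale decides the primary conclusion

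*Protocol article*

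**What the plan says.** Section 2 (Objectives) gives one primary objective with two parts: the AI's suggested level of care against the healthcare team's, and the effectiveness of the stratified care model. Of both it says: "This will be assessed using the change in the severity of depressive symptoms", to be measured by PHQ-9 and QIDS. Quality of life and functioning on the AQoL-8D are added in the same sentence. All three are taken from the start to the end of the 13-session program. None is ranked above another, and no rule for combining them is given.

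Section 4 (Statistical analysis) applies one level throughout: all analyses "will consider a significance level of 0.05 and 95% confidence intervals". Section 4.1 plans a "linear mixed-effects model for each questionnaire to compare clinical outcomes within and between groups and times", which means three models for the three primary scales.

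The only adjustment is the sentence that closes Section 4.1: "Bonferroni corrections will follow the ANOVA analyses in *post hoc* analyses". The article names ANOVA in two places. Section 4.1 uses a "two-way analysis of variance (ANOVA) to compare the number of completed sessions across participant groups and care levels", and Section 4.3 uses a two-way ANOVA for costs. Section 2 lists both outcomes under the secondary objectives.

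Section 3.10 bases the sample size on PHQ-9 alone, but nowhere does the article call PHQ-9 the single primary outcome.

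**The concern.** Three scales have equal standing under the primary objective, and each is tested at the full 0.05. The one correction in the text attaches to analyses of secondary outcomes. Nothing says whether one scale is enough, whether all three must agree, or which prevails if they disagree.

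Two things are at stake. First, if a significant result on any scale is taken as a primary result, the chance of a false one exceeds 5%. Second, and more important here, the scales may disagree. PHQ-9 might show no difference between arms while QIDS or AQoL-8D shows one, or the reverse. With no rule fixed beforehand, the trial's primary conclusion would depend on which scale is put forward once the results are known.

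**Working it through.** **The plan's own figure (Section 3.10).** This shows which scale the trial is sized on and for what comparison.

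- Inputs: PHQ-9 mean 16.2 before and 11.48 after, SD 5.45, power 0.8, completion 45%.
- Effect size: (16.2 − 11.48)/5.45 = 0.866; the article states 0.86.
- Paired t-test, two-sided 0.05, power 80%: n = 12.7, so 13. The stated 14 is one above this, with 84% power.
- 14/0.45 = 31.1; the article states 31 (strict rounding up gives 32).
- 31 × 3 intensities × 2 arms = 186, as stated.

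The stated size is reproduced to within a patient or so per cell. It rests on one scale, at 0.05, and on a within-group change. It makes no allowance for three scales and is not a calculation for the difference between arms.

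**Error across the scales.** Inputs: three scales (Section 2), 0.05 for each (Section 4) and one contrast per model. The level is taken as two-sided because it is paired with 95% confidence intervals. The article gives no correlation between the scales, so a range is assumed.

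- Three independent scales: 1 − 0.95³ = 14.3%. The upper bound is 3 × 0.05 = 15%.
- Two independent scales: 1 − 0.95² = 9.75%.
- Correlated scales: simulated as equally correlated two-sided z tests with no true difference on any scale, 4 million draws per correlation.

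| Assumed correlation | Any of three significant | Any of two significant | All three significant |
|---|---|---|---|
| 0 | 14.3% | 9.8% | 0.01% |
| 0.3 | 13.6% | 9.5% | 0.09% |
| 0.5 | 12.6% | 9.1% | 0.3% |
| 0.7 | 10.9% | 8.3% | 0.9% |
| 0.8 | 9.8% | 7.8% | 1.4% |
| 0.9 | 8.3% | 7.0% | 2.3% |

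One contrast per scale is the smallest possible count, since each model also tests care level, time and interactions. The last column shows how much depends on the missing rule: the same three tests give 8% to 14% under one rule and below 5% under the other.

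**Reach of the Bonferroni sentence.** Read literally, it covers sessions and costs only. Read loosely, with the factorial mixed models counted as ANOVA, it adjusts post hoc comparisons within a model. On neither reading is there an adjustment across the three questionnaires.

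**The case against.** The strongest reply is that Hypothesis 1 claims comparability. A false significant difference between arms counts against that hypothesis, so the 8% to 14% is not a rate of false success. This stands for the arm comparison. A stricter level on the arm contrasts would even make a lack of difference easier to report, so a blanket correction would push the wrong way. The reply does not cover the second part of the primary objective, the effectiveness of the stratified care model, where a significant result would favour the claim.

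Three further replies have some force:

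- **The any-scale rule is assumed.** Section 2 joins the scales with a plain conjunction and never says that one suffices. This stands. A reader might infer that the primary error rate is simply not 5%, but the article does not support that, because the rate depends on a rule it does not state.
- **Only two scales bear on Hypothesis 1.** It names depressive symptoms, which Section 3.9 assigns to PHQ-9 and QIDS. This stands too, and the two-scale ceiling is 9.8%. But the primary objective includes AQoL-8D where the hypothesis does not, which is itself part of the uncertainty about what decides.
- **A hierarchy may sit in a full analysis plan.** It may, and a general 0.05 does not exclude one. Still, this article is not merely silent: it gives three scales equal primary standing, fixes the level for every analysis and says where correction applies.

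**Conclusion.** The point holds in a limited form. The article has three unranked primary measures, a separate test at 0.05 for each, and no stated control or decision rule across them. If any one scale could carry a primary result, the chance of at least one false difference would be about 8% to 14% for three scales, or 7% to 9.8% for the two depression scales. These ranges assume correlations from 0.9 down to 0 and one contrast per scale. Under an all-three rule the rate would be below 5%, and the cost would fall on power instead.

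A reader might go further and conclude that the trial has a two- to threefold risk of falsely claiming that the AI matches the team. The article does not support that. The error computed here is a false difference, and a claim of comparability would need a margin, which the article does not give. That is a separate gap.

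The main harm is the freedom to choose among discordant scales after the results are seen. It is inexpensive to remove.

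**What to change.** In Sections 2 and 4.1, name one primary outcome: the AI-versus-team difference in PHQ-9 change from baseline to week 13, estimated from the planned mixed model and reported with its 95% confidence interval. Week 13 is a scheduled assessment for all three scales (Section 3.9) and matches the start-to-end period in Section 2. Make QIDS and AQoL-8D secondary, reported with confidence intervals as supportive evidence.

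Apply a multiplicity adjustment such as Holm only where a significant difference or effect is claimed on the secondary scales. Do not apply it to arm contrasts used to argue comparability.

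Do not cite Section 3.10 as power for the new primary contrast, because it sizes a within-group paired change. The change also does not supply a comparability margin.

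The cost is that QIDS and AQoL-8D can no longer carry the primary claim, which takes the quality-of-life component out of the primary objective. Recruitment began in December 2022, so the change of primary outcome must be documented as an amendment before analysis. It needs no extra participants or visits.

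The alternative of keeping three co-equal scales with Bonferroni, at 0.05/3 = 0.0167 each, costs more. On the article's own paired-test basis it needs 18 evaluable per cell instead of 14, so 18/0.45 = 40 per cell and 40 × 6 = 240 in total against 186. With 14 evaluable kept, power falls from 84% to 68%.
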